#### Unlikely to be related

Generally, the cases listed below are considered unlikely to be related:

- - Evidence of investigational product administration.
  - A higher possibility that an adverse event is due to reasons other than investigational product administration.
  - Negative or dubious results after investigational product discontinuation or dose reduction (if applicable).
  - Negative or dubious results after investigational product re-administration.

1. **Not related**
   - The subject failed to receive the investigational product.
   - No logical temporal order between investigational product administration and the adverse event incidence.
   - The presence of other evidence that can clearly explain the reason for the adverse event incidence (e.g. bleeding from a surgical site).
   - Not likely (e.g. the patient collided with a motorcycle, but there is not enough proof that the investigational product causes enough loss of proprioception to cause the event, or a cancer that is found days after investigational product administration).

#### Not assessable

There is insufficient or paradoxical information that cannot be supplemented or confirmed.

The following points must be considered in order to evaluate the association between the investigational drug and any adverse events:

- - Temporal continuity after drug administration: An adverse event must occur after investigational product administration. The time interval after investigational product administration to the onset of the adverse event must be evaluated based on the clinical condition of the event.
  - Recovery after drug discontinuation and / or recurrence after re-administration: the reaction of the subject after drug discontinuation and drug re-administration must be evaluated (re-administration must be considered from the point of view of normal clinical steps for the event in question).
  - Baseline, co-existing, and co-morbid disease: reports on each adverse event must be evaluated based on the characteristics and progression of the disease being treated and other diseases.
  - A co-administered drug or treatment: other drugs or treatments administered to the subject may be associated with the event in question and must also be evaluated.
  - A reaction or trend already known to be related to this class of drug: clinical / pre-clinical.
  - Exposure to physical and / or psychological stress: exposure to stress can lead to a change in adverse events and provides a logical and more accurate reason for an adverse event.
  - The pharmacological and pharmacokinetic properties of the drug: the pharmacokinetics of the investigational product (absorption, distribution, metabolism, excretion) must be considered in conjunction with a subject’s medication history.

#### Laboratory abnormalities and other findings outside of the reference range

All laboratory tests and results must be recorded on the case report form. The cases listed below must be treated as adverse events and recorded and reported separately on the adverse event report form within the case report form.

- - Laboratory values that lead to study discontinuation.
  - Clinical symptoms.
  - Subject requires treatment.
  - Other cases deemed clinically relevant by the investigator: clinically significant laboratory abnormalities or other measured values that are found after investigational product administration or that have existed at study commencement, but have been exacerbated after study commencement, are considered to be adverse events or serious adverse events. However, clinically important findings which existed at study commencement, but which were not exacerbated after investigational product administration are not considered adverse events or serious adverse events.

#### Serious adverse events

Serious adverse events (SAEs) refer to incidences of medical events that were not intentional at an arbitrary dose of the investigational product, and include the following cases:

- - Death.
  - A life-threatening situation (a “life-threatening situation” is defined as a case in which a subject is at risk of death during an adverse event; it is not a situation which can theoretically lead to death if the adverse event worsens).
  - A need for hospitalization or prolongation of hospitalization: this does not include hospitalization for treatment related to the protocol or for normal clinical treatment. It refers to official hospitalization and excludes emergency room visits (however, a stay exceeding 24 hours is considered hospitalization). It does not include hospitalization pre-scheduled before study commencement, hospitalization for a pre-existing condition that does not worsen during the study period, or hospitalization for aesthetic purposes (e.g. cosmetic surgery). Hospitalization or prolongation of hospitalization at the subject’s will, and not due to medical reasons, is not considered an SAE.
  - Permanent or serious disability or dysfunction.
  - Fetal deformity or abnormality.
  - Other medically important adverse events: a medically important event can qualify as an SAE even if it does not cause death, is not life-threatening, or does not require hospitalization. Such cases include those that may endanger the subject, according to appropriate medical evaluation, or that require medical or surgical treatment to prevent the above SAE. Examples include allergic bronchospasm that requires at-home or emergency intensive treatment, blood dyscrasia that does not merit hospitalization, convulsions, and drug dependency or misuse. Suspected infection via the investigational product will also be treated as an SAE. All such cases must be reported swiftly, as detailed in Section 6.3.1.4.

#### Reporting and evaluation of adverse events

At each visit, the subject will be asked about their health status. During the adverse event reporting period of the study, all undesirable status changes reported by the subject or observed by the investigator will be recorded as adverse events. All information regarding all adverse events experienced by a subject during the adverse event reporting period (stated below) will be recorded consistently, completely, accurately, and continuously in case report form. SAEs will be recorded additionally in the SAE report form, as per Section 6.3.1.1.4, and reported separately. For each adverse event, the description, duration (including date of occurrence and date of resolution: the timing must also be known if the timing of the adverse event incidence relative to the investigational product administration time is also important), seriousness, association with the study treatment, other suspected causes, treatment given, other treatments (including investigational product dose adjustment and discontinuation), and progress will be reported. SAEs must be strictly identified during the study period and recorded and reported according to the appropriate category.

#### Definition of the adverse event reporting period

The adverse event and SAE reporting period commences on the date of subject enrollment (the date that the consent form is signed) and continues until the end of the follow-up period after treatment. If a continuing adverse event is observed at the visit at the end of the study, the subject will be monitored until the adverse event improves or stabilizes.

#### Reporting process for SAEs

The investigator will inform the sponsor (or proxy) and the pharmacovigilance personnel for the investigational product distributor ([name], Department of Orthopedics, Severance Hospital) immediately (within 24 hours of becoming aware of an adverse event), by fax or email, of all new SAEs that occur during this period.

The pharmacovigilance personnel for [name] (Department of Orthopedics, Severance Hospital) can be contacted as follows:

**Email:** [**[contact]**](mailto:[contact])

#### [contact]

**[contact]**

An SAE that has already been reported must also be followed up using the same process and deadline as for a new adverse event.

All SAE reports will be filled out by the investigator, in accordance with the SAE report form, and processed.

The information on an SAE report form must always concur with the appropriate section of the case report form. If the investigator / reporter is asked for follow-up information (i.e. additional information, progress, final evaluation, and / or the relevant record by request) or receives the sponsor’s query regarding the SAE, it must be handled within the same deadline as the first report. This is crucial to allow the sponsor to evaluate the SAE and meet the legal processing deadline for prompt safety reporting.

Under certain exceptional circumstances the sponsor may contact the investigator directly to clarify or discuss a particularly urgent situation, but follow-up observation is normally requested by the monitoring agent in charge of the study.

#### Safety reporting to government authorities, the institutional review board (IRB), and the investigator

If the investigator reports an SAE (in particular, death) in a subject to the IRB, the report must follow the SAE reporting criteria of the said IRB. According to the ICH GCP, the sponsor must notify the investigator if “a case that may negatively affect a subject’s ability to undergo the study or changes the IRB approval status on the continuation of the study” occurs. In particular, according to the relevant regulations, the sponsor must inform the investigator of any suspected unexpected serious adverse reaction (SUSAR). The investigator must store safety-related reports within the investigator’s site file. Safety reporting must comply with local regulations for safety reporting to the investigator. If mandated by law, the sponsor can directly report to the IRB, and such a report will be documented. If not mandated by law, the investigator must directly report the safety information supplied by the sponsor to the IRB, and copies of all communication records regarding this issue must be kept within the investigator’s site file. The sponsor must report safety-related issues to the health authorities, according to the relevant law and regulations. For local studies, SUSAR reports must be conducted according to the Pharmaceutical Affairs Act. According to this Act, any SUSAR that is fatal or life-threatening must be reported to the MFDS within 7 days of the sponsor becoming aware of it, and, in such a case, the sponsor must report the details of the SUSAR within 8 days of the first report date. All other SUSARs must be reported within 15 days of the sponsor being made aware of them.

#### Monitoring of a subject’s adverse event

The investigator must monitor and follow up a subject who has an adverse event that may be associated with the investigational product during the study period until disappearance of the said adverse event or confirmation of final progress, unless follow-up becomes impossible. The investigator must do due diligence to confirm the information regarding the adverse event and must document such information. The investigator is responsible for appropriate additional treatment and follow-up observation of the adverse event. The sponsor must actively follow up adverse events occurring during the study period and collect all relevant information. However, for SAEs, such measures must continue until the resolution of the SAE or confirmation of final progress, while for all other adverse events, such measures will only continue until database lock.

## Exposure of pregnant women

A pregnancy that is deemed by the investigator to be associated with the study treatment (as a result of drug interaction with contraceptives) will be considered an adverse event. However, all pregnancies that occur during the period defined in 6.4.1.3 must be recorded in the adverse event section of the case report form. This applies to both the female subjects and the female partners of male subjects. The investigator must promptly inform the sponsor within 24 hours of becoming aware of the pregnancy using the attached pregnancy report form, in accordance with the process stated in Section 6.4.1.4.

The investigator must actively follow up and record the progress of the pregnancy, even if the subject is removed from the study, and must report the results to the sponsor. If the progress is abnormal and the abnormality persists within the subject or child / fetus, this must be reported using the SAE report form. All abnormal progress related to the pregnancy must be promptly reported by the methods defined in Section 6.3.1.4, and normal progression of the pregnancy must be reported as soon as possible, within 45 days of delivery.

Subjects who become pregnant during the study period must discontinue the investigational product. The sponsor must be notified without delay, and the subject must follow the pre-specified process.

## Laboratory tests

Before the investigational products are delivered to each site, the reference ranges for laboratory values must be conveyed to the sponsor or the sponsor’s proxy. If the reference range changes during the study period, the sponsor or sponsor’s proxy should be notified. The investigator must prevent errors by confirming the identity of the samples collected for laboratory tests.

#### Table 2. List of Laboratory Safety Tests

| **Hematology** | **Serum Chemistry** |
| --- | --- |
| Hemoglobin (Hgb) | Alanine aminotransferase (ALT) |
| Hematocrit (Hct) | Aspartate aminotransferase (AST) |
| RBC count | Blood urea nitrogen (BUN) |
| Platelet | Creatinine |
| WBC with differential count | Glucose |
|  | Total bilirubin |

## Vital signs, physical examination, and other evaluations

A general physical examination will be conducted during the screening and final visits. Vital signs include blood pressure, pulse rate, respiratory rate, and body temperature. The physical examination and vital signs results will be recorded in the case report forms.

## Efficacy evaluation

## Primary evaluation

This study will use the Leeds Dyspepsia Questionnaire (LDQ) as its primary evaluation method,.

The LDQ is a method proven to evaluate the severity and treatment response of eight symptoms of gastrointestinal disorders. (25)

The 8 symptoms evaluated are:

1. Indigestion (pain in the upper abdomen).
2. Heartburn (a burning feeling behind the breast bone)
3. Food or drink stuck behind the breast bone
4. Regurgitation (an acid taste coming up into the mouth from the stomach)
5. Burping or belching
6. Nausea
7. Vomiting
8. Excessive fullness

Each of these symptoms is rated on the Likert scale from very mild, to mild, moderate, severe, and very severe.

## Secondary evaluation

As secondary evaluation endpoints, the GSRS, pain VAS, and EQ-5D will be used.

- The GSRS (Gastrointestinal Symptom Rating Scale) consists of 15 short answer questions that can indicate a high correlation with gastroesophageal reflux disease, functional dyspepsia, and irritable bowel disease. (26, 27, 28)
- The VAS (visual analogue scale) will be used to evaluate the osteoarthritic pain experienced by the subjects. The VAS is a simple method that is widely used for pain evaluation in osteoarthritis patients. It has proven correlation with the survey-based Likert scale. (29)
- EQ-5D is a widely-used tool for the measurement of quality of life and health status. It includes the five categories of mobility, self-care, usual activities, pain / discomfort, and anxiety / depression. Each item is measured using the VAS, indicating subjective health status on a thermometer-shaped scale, as well as by multiple choice questions that evaluate health status as one of the following three stages: “no problem”, “some problems”, and “extreme problems”.

The study will also evaluate the incidence rate of gastrointestinal adverse events and the discontinuation rate due to gastrointestinal adverse events.

As an ancillary method to evaluate the pain control of the experimental drug and comparator, this study will also evaluate ancillary and rescue drug use after 8 weeks of oral administration of the study drugs, the average number of days of use, the average amount used per day (total amount used / days used) and the average amount of use during the study period (total amount used / study duration).

This study will also include compliance analysis. Compliance is defined as ‘(the actual number of administrations) / (the planned number of administrations)*100’, and patients with a compliance rate of 80% or above will be included in the PP (per-protocol) group analysis.

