## Secondary evaluation endpoint

- Average LDQ after 12 weeks of oral administration of the investigational product.
- Average change in the GSRS from baseline after 12 weeks of oral administration of the investigational product.
- Incidence rate of GI adverse events (dyspepsia, diarrhea, nausea, abdominal pain, heartburn) after 12 weeks of oral administration of the investigational product.
- Discontinuation rate due to GI adverse events after 12 weeks of oral administration of the investigational product.
- Average change in the pain VAS from baseline after 12 weeks of oral administration of the investigational product.
- Average change in the average EQ-5D score from baseline after 12 weeks of oral administration of the investigational product.
- Drug compliance after 12 weeks of oral administration of the investigational product.
- Ancillary and rescue drug use after 12 weeks of oral administration of the investigational product: average number of days used, average daily amount used (total amount used / total number of days used), and average amount of use during study participation (total amount used / study duration).
- Incidence, frequency, and characteristics (clinical presentation, severity, result, etc.) of adverse events after 12 weeks of oral administration of the investigational product.
- Results of physical examination, vital signs, and laboratory tests after 12 weeks of oral administration of the investigational product.

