#### Gastrointestinal Symptom Rating Scale (GSRS)

Please read the following and check the number that corresponds to your experience over the past 3 months.

- 1.
[figure not shown]

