**Abdominal pain**

This means pain in the entire area of the abdomen (below the ribs, not in the chest).

[0]. No pain, or momentary pain.

[1]. Pain or discomfort that occurs intermittently and hinders activity.

[2]. Prolonged pain or discomfort that required alleviation and hinders many social activities.

[3]. Severe and debilitating pain that affects all social activities.

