#### Heartburn

[figure not shown]
This means burning pain in the esophagus area (post-sternal).

[0]. No burning, or momentary burning.

[1]. Short-term discomfort that occurs intermittently.

[2]. Prolonged discomfort that occurs often and requires alleviation.

[3]. Prolonged discomfort that is temporarily alleviated by antacids.

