#### Acid regurgitation

This means unpleasant reflux of acidic fluid from the stomach towards the chest.

[0]. No regurgitation, or momentary regurgitation.

[1]. Bothersome regurgitation that occurs intermittently.

[2]. Regurgitation that occurs 1-2 times a day and requires alleviation.

[3]. Regurgitation that occurs many times a day and is only temporarily and ineffectively alleviated by antacids.

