#### Eructation

This is expulsion of gas through the mouth without rumination, which is regurgitation of gastric contents, and vomiting.

[0]. No eructation, or momentary eructation.

[1]. Bothersome eructation that occurs intermittently.

[2]. Frequent eructation that hinders some social activities.

[3]. Frequent eructation that severely hinders social activities.

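### Section 6.4.2 describes a 15-question GSRS, but the form in Appendix 3 has eight items and none on stool or bowel habit

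*Protocol*

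**What the plan says.** Section 6.4.2 names the GSRS among the secondary measures and says it "consists of 15 short answer questions that can indicate a high correlation with gastroesophageal reflux disease". The same sentence adds functional dyspepsia and irritable bowel disease.

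Comparison of the arms on the GSRS is the first secondary purpose in Section 3. The endpoint in Section 7.3.2 is "Average change in the GSRS from baseline after 12 weeks of oral administration of the investigational product", and Section 7.5.3 analyses it within and between arms. Neither section names a short form, a subset or a scoring rule.

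Appendix 3 contains the form that subjects complete at Visits 2 and 3. It asks them to "check the number that corresponds to your experience over the past 3 months". Eight items follow, each with options 0 to 3. The last is eructation, explained with the words "This is expulsion of gas through the mouth without rumination". The EQ-5D starts directly after it.

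**The concern.** The description and the form cannot both be right, and an analysis plan cannot settle the matter later, because it cannot recover questions that were never asked. If the form is used as printed, the trial would report a GSRS change under the name and 15-question description of a scale that subjects did not complete.

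Apart from the LDQ, the GSRS is the only patient-rated gastrointestinal symptom scale in the trial. Its value as a secondary measure lies in what it adds to the LDQ. The absent content matters because Section 5.3.4.1 lists diarrhoea and constipation as common with the experimental drug, and Section 5.3.5.1 gives diarrhoea at 5.6% with the control drug. Without a bowel-habit item, the printed form also gives little support to the link with irritable bowel disease drawn in 6.4.2.

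**Working it through.** **1. Count.** Stated in 6.4.2: 15 questions. Printed in Appendix 3:

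| Item on the GSRS form | Counterpart in the LDQ (Section 6.4.1, Appendix 2) |
| --- | --- |
| Abdominal pain | Indigestion, in part (the LDQ item is upper abdomen only) |
| Heartburn | Heartburn |
| Acid regurgitation | Regurgitation |
| Epigastric burning | Indigestion (its margin note includes burning) |
| Nausea and vomiting | Nausea; vomiting |
| Borborygmus | None |
| Abdominal distension | Excessive fullness |
| Eructation | Burping or belching |

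The count is 8, so the stated 15 is not reproduced. The shortfall is 15 − 8 = 7, or 7/15 = 47%; the form carries 8/15 = 53% of the stated number. Splitting nausea and vomiting into two gives only 9, so no way of counting closes the gap.

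**2. Content.** No item concerns stool frequency, consistency, urgency or incomplete evacuation. Seven of the eight items have a full or partial LDQ counterpart; only borborygmus has none.

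**3. Score range.** Eight items at 0 to 3 give a total of 0 to 8 × 3 = 24. Fifteen items would give 0 to 15 × 3 = 45, but only on the assumption that the seven absent items are scored in the same way, which the protocol does not say.

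**4. Recall period.** Take three months as about 91 days (an assumption) and Day 1 as the first treatment day. The days of recall before Day 1 are then 91 minus the visit day. The protocol gives two windows for Visit 3:

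- Day 84 to 87 (Section 6.1 and Appendix 1): 91 − 87 = 4 to 91 − 84 = 7 days.
- Day 84 ± 7, that is Day 77 to 91 (Synopsis and Figure 1): 91 − 91 = 0 to 91 − 77 = 14 days.

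As a share of the recall, this is 4/91 = 4% to 7/91 = 8% for the first window, and 0% to 14/91 = 15% for the second. The LDQ, by contrast, asks about the last four weeks.

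**5. Reach.** The sample size uses only LDQ inputs: 2 × 0.65² × (1.96 + 0.842)² / 0.4² = 41.5, hence 42 per arm, and 42/0.8 = 52.5, hence 53. Nothing here changes it.

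**The case against.** The endpoint in Sections 7.3.2 and 7.5.3 refers only to the GSRS, without an item count, and a change score can be computed from the printed form. That stands. A reader might infer that the GSRS endpoint cannot be measured at all, but the documents support only the narrower statement that the 15-question scale of 6.4.2 cannot be obtained.

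A reader might also take the form to be purely upper-gastrointestinal. It is not: the pain item covers the whole abdomen, and borborygmus is not confined to the upper part. The accurate description is that there is no stool or bowel-habit item.

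Nor would the trial miss diarrhoea and constipation altogether. Diarrhoea is a named component of the gastrointestinal adverse event endpoint, which is compared between arms, and constipation would appear in the adverse event tables by preferred term. What is lost is the patient's own rating of change in these symptoms.

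On recall, a reader might infer that 8-15% of the recall period always lies before treatment. Those figures hold only for visits from Day 77 to 84, the early part of the wider of two conflicting windows. The recall wording is the same in both arms, and no effect on the comparison is shown. The overlap need not fall in a washout either, since Appendix 1 allows screening and randomization on the same day.

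Finally, items could have been lost when the form was converted to text: its numbering is irregular and some pictures are absent. This cannot be fully excluded. However, each such gap lies beside an item or instruction that is present, and the form runs on without a break into the EQ-5D.

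**Conclusion.** The contradiction stands. Section 6.4.2 describes 15 questions and Appendix 3 prints eight, with no bowel-habit item and no short form named anywhere. As printed, the trial can deliver only an eight-item change score on a 0-24 total that largely repeats the content of the LDQ.

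The consequence is limited to one of the ten secondary endpoints listed in Section 7.3.2, although it is the first secondary purpose. The primary LDQ analysis, the margin and the sample size are untouched. The recall overlap is a minor related point: about 4-7 days or 0-14 days, depending on which Visit 3 window applies and on taking three months as about 91 days. The conclusion on the items rests on the Appendix 3 form being complete as printed.

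**What to change.** Before first use, replace the GSRS page in Appendix 3 with the 15-item form that Section 6.4.2 describes.

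If the printed form is already in use, keep it for consistency and correct the text. State in Sections 3, 6.4.2, 7.3.2 and 7.5.3 that an eight-item version without bowel-habit items is used, give its scoring, and remove the 15-item description. Do not label it an upper-gastrointestinal subset.

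In the same revision, shorten the recall period so that at Visit 3 it lies within the treatment period, with the same wording at both visits. State one Visit 3 window throughout.

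The cost is one longer questionnaire page at two visits, or wording changes only if the eight-item version is kept. A revised form also needs IRB approval under Sections 8.5 and 9.5.

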## Safety evaluation

The safety of the investigational products will be evaluated by recording, reporting, and analyzing the subjects’ baseline comorbidities, adverse events, physical examination results (including vital signs), and laboratory test results. The severity of the adverse events that may occur after the administration of the investigational products will be evaluated using the CTCAE (Common Terminology Criteria for Adverse Events).

After consent has been given, a comprehensive evaluation of drug toxicity, including the adverse events experienced by the subjects, will be conducted throughout the duration of the study. All personnel involved in the study must report all adverse events reported by the subjects and recognized by the investigator (refer to section 6.3.1.2, “Reporting and evaluation of adverse events”). Refer to Sections 6.3.1.4 and 6.3.1.5 for the deadline for adverse events reporting.

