## Definition of analysis sets

#### Target population

This study will be conducted on osteoarthritis patients of ≥50 years who can perform normal physical activity during the study period, with a pain VAS of 40 mm or more.

**Safety evaluation set: A population in which at least one safety follow-up observation is made after randomization and investigational product administration.**

**Full Analysis (FA) set: A population in which at least one efficacy evaluation is performed after randomization and investigational product administration.**

**Per-Protocol (PP) set: A population in which at least one efficacy evaluation is performed after randomization and investigational product administration, and in which there is no major protocol violation (violation of inclusion / exclusion criteria, violation of compliance). A compliance rate of 80% is used as the reference.**

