## Statistical analysis plan

## General considerations

Efficacy data obtained from the subjects in this study will be analyzed in the FA and PP sets. Safety data will be analyzed in the Safety evaluation set. Considering that this is a non-inferiority study, the primary efficacy endpoint will be analyzed in both the FA and PP sets, according to ICH guidelines.

All statistical sets, excluding the primary efficacy endpoint, will be subjected to two-sided tests with a significance level of 5%.

Missing data will be replaced using a multiple imputation method. No interim analysis will be performed.

Co-administered drugs will be recorded in ATC terminology, and adverse events and medical history will be standardized to SOC (system organ class) and PT (preferred term) using a Medical Dictionary (MedDRA or WHOART).

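### GI adverse-event endpoints have conflicting analysis sets, compliance is routed only to FA and PP, and a PP analysis of GI discontinuation or compliance is circular

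*Protocol*

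**What the plan says.** Section 6.4 of the protocol is headed "Efficacy evaluation". Its subsection 6.4.2 states: "The study will also evaluate the incidence rate of gastrointestinal adverse events and the discontinuation rate due to gastrointestinal adverse events". The same subsection adds: "This study will also include compliance analysis". It defines compliance as actual over planned administrations, times 100, and makes 80% or above the condition for the PP analysis. Section 7.4 repeats the threshold in the PP definition: "A compliance rate of 80% is used as the reference". The FA definition there has no compliance criterion; it asks for at least one efficacy evaluation after dosing.

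Section 7.5.1 allocates data to sets: "Efficacy data obtained from the subjects in this study will be analyzed in the FA and PP sets" and "Safety data will be analyzed in the Safety evaluation set". Section 6.3 lists adverse events as safety data: "The safety of the investigational products will be evaluated by recording, reporting, and analyzing the subjects’ baseline comorbidities, adverse events".

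Section 7.5.3 gives the tests for GI adverse-event incidence, GI discontinuation and compliance, but names no analysis set for any of them. GI events, GI discontinuation and compliance are stated secondary purposes in the Synopsis and Section 3, listed apart from overall safety.

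**The concern.** Two separate problems follow from these rules.

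First, GI adverse-event incidence and GI discontinuation are efficacy items by their place in 6.4.2 and safety items by 6.3. Under 7.5.1 the first reading leads to FA and PP, the second to the Safety evaluation set. Nothing in 7.5.3 settles which applies. Compliance appears only under efficacy, so the general rule takes it to FA and PP.

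Second, PP is an unsuitable population for two of these endpoints. Stopping drug early lowers compliance, and compliance below 80% removes the subject from PP. A GI discontinuation rate in PP is therefore computed after most of the subjects who had the outcome have been taken out. A compliance comparison in PP compares a variable that cannot fall below 80% in either arm.

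In a trial about gastroprotection, a PP table of GI stopping would tend to show similar arms even where stopping truly differed.

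**Working it through.** **The plan's own figure.** The sample size reproduces and is not in dispute. With SD 0.65, margin 0.40, one-sided alpha 0.025 and 80% power (Section 7.1): 2 × 0.65² × (1.96 + 0.842)² / 0.40² = 41.46, rounded up to 42 per arm. Allowing for 20% drop-out, 42 / 0.80 = 52.5, rounded up to 53 per arm.

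**Which set each endpoint reaches**

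| Endpoint | By 6.4.2 and 7.5.1 | By 6.3 and 7.5.1 |
| --- | --- | --- |
| GI adverse-event incidence | FA and PP | Safety set |
| GI discontinuation | FA and PP | Safety set (as an adverse-event outcome) |
| Compliance | FA and PP | not listed in 6.3 |

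**Stop day at which a subject leaves PP.** Inputs from the protocol are the 80% threshold and the 12-week (84-day) period. Assumptions are that planned doses cover all 84 days and that adherence is full until stopping. Compliance is then stop day / 84, and it is below 80% when the stop day is before 0.80 × 84 = 67.2. If adherence before stopping is below 100%, the cut-off moves later: 67.2 / 0.95 = Day 70.7 and 67.2 / 0.90 = Day 74.7.

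**Share of stoppers removed from PP.** The documents give no stop times, so a range is needed (full adherence until stopping):

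| Assumed stop times over 84 days | Formula | Share removed |
| --- | --- | --- |
| Uniform | 67.2 / 84 | 80% |
| Late-weighted (linearly rising density) | 0.80² | 64% |
| Early-weighted (truncated exponential, scale s = 84 days) | (1 − e^(−67.2/s)) / (1 − e^(−84/s)) | 87% |
| Same, s = 56 | as above | 90% |
| Same, s = 28 | as above | 96% |
| Same, s = 14 | as above | 99% |

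**Effect on the GI discontinuation rate.** Take 53 per arm, assumed true rates of 10% and 5%, and no other exclusions. With share f removed, the PP rate is 53p(1 − f) / (53 − 53pf).

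- f = 0.80: 1.06 / 48.76 = 2.2% and 0.53 / 50.88 = 1.0%. A 5.0-point difference becomes 1.1 points.
- f = 0.64: 3.9% and 1.9%, a difference of 2.0 points.
- f = 0.95: 0.6% and 0.3%, a difference of 0.3 points.

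**Compliance.** No simulation is needed. Every PP member has compliance of at least 80% by definition, so the lower part of the distribution, where the arms could differ, is absent.

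**FA.** The compliance rule removes nobody. However, FA needs an efficacy evaluation after dosing, and Section 6.1 schedules these only at Visit 3 and the early termination visit. Section 4.5.1 asks for the Visit 3 assessments after early withdrawal only where possible. A subject who stops for a GI event and is seen only at an additional visit, whose suggested content includes no symptom questionnaires, would not be in FA. The documents do not allow this loss to be counted.

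**The case against.** The strongest reply is that no sentence assigns these endpoints to FA or PP. The efficacy route joins a section heading to a general rule, while Section 6.3 sends adverse events to the Safety evaluation set, which is the set wanted here. Being a secondary endpoint proves nothing, since Section 7.3.2 also lists vital signs and laboratory tests. This stands: for the GI endpoints the defect is a conflict, and a reader who infers that the protocol clearly places them in FA and PP goes further than the text. It does not help compliance, for which Section 6.3 offers no competing route. Equally, compliance cannot be said to have two conflicting populations.

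A reader might also infer that the 80% rule strips GI stoppers from the efficacy analyses in general. It does not: Sections 6.4.2 and 7.4 tie the threshold to PP, and the FA definition contains no such criterion. (Section 4.5.1 lists low compliance among violations leading to exclusion, with an unclear parenthesis about PP; it does not alter the FA definition.) FA results would be reported beside PP, so a true difference need not disappear from the report.

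The size is also open. Event rates and stop times are assumed. Section 6.4.2 says only planned administrations; if these were counted only to the stop date, early stopping would not by itself remove anyone from PP. Section 7.5.3 describes compliance over the 12 weeks, which favours the full-period reading without stating the denominator. Nothing is quantified for GI adverse-event incidence, because subjects with an event who keep taking drug stay in PP.

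Finally, an unseen SAP might name the sets. The protocol is not silent, though: it fixes an allocation rule, and that rule leads to an analysis conditioned on the outcome.

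**Conclusion.** The point holds in this form: the GI endpoints have conflicting analysis sets, compliance falls by rule to FA and PP, and the PP analysis is circular for GI discontinuation and for compliance. Truncation of compliance at 80% is certain from the definitions. The loss of GI stoppers from PP rests on a full 12-week denominator and full adherence until stopping. On that basis it is about 80% for uniform stop times and 64% to 99% over the other distributions tried, so it is a majority in every case. The shrinkage from 10% v 5% to about 2.2% v 1.0% is an illustration at assumed rates, not a forecast. FA escapes the 80% rule but may lose an unknown number of stoppers who have no early-termination efficacy assessment. These are secondary endpoints and the primary non-inferiority conclusion is untouched, but the change should be made.

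**What to change.** State in Sections 6.4.2 and 7.5.1 that GI adverse-event incidence, discontinuation due to GI adverse events and compliance are analysed in the Safety evaluation set and are not analysed in PP. In the compliance definition (6.4.2, repeated in 7.5.3), state that the denominator is the full planned 12-week schedule, including for subjects who stop early.

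The cost is one or two sentences and fewer PP tables. No extra data or subjects are needed. The primary analysis and the sample size (42 evaluable, 53 enrolled per arm) stay as they are.
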